#### Statistical Analysis

Baseline characteristics will be summarized by randomized group using counts and percentages for categorical variables and means and standard deviations for continuous variables, or medians and interquartile ranges for skewed variables. Because treatment assignment is randomized, baseline characteristics will be described primarily to assess sample comparability rather than to guide significance-based inference.

Primary efficacy analyses will compare randomized groups from baseline to 12 weeks, before the waitlist group receives the intervention. The treatment effect for the primary outcome, a 4-item heart attack response preparedness score, will be estimated using constrained longitudinal data analysis (cLDA) implemented via linear mixed models (LMMs) [37]. Consistent with the randomized design, the models will constrain the mean scores for the treatment and control groups to be equal at baseline. The primary outcome will include categorical fixed effects for time and a time-by-treatment group interaction term. The primary model contrast of interest is the coefficient for this interaction term at the 12-week follow-up, representing the baseline-adjusted between-group difference. To account for the within-subject correlation between baseline and follow-up, the cLDA models will use an unstructured covariance matrix, allowing variances and correlations to differ over time.

The 4 individual preparedness items will be analyzed as prespecified key secondary outcomes, subject to the hierarchical gatekeeping procedure described above. The primary efficacy analysis and all key secondary analyses will be based on the baseline and 12-week assessments only. Although the individual items are ordinal, the primary analysis will use the same linear cLDA framework to facilitate interpretation of mean differences and support model stability [38]. Robustness of this linear approximation will be evaluated in sensitivity analysis using ordinal logistic mixed-effects models for each individual item.

All analyses will follow the intent-to-treat (ITT) principle, with all randomized participants in the groups to which they were assigned. Missing data will be addressed using multiple imputation by chained equations (MICE) to preserve the repeated-measures structure of the data. Multiple imputation was selected in part to address occasional missing item-level responses when constructing the composite preparedness score. Imputation will be conducted in a wide format, using predictive mean matching (PMM) so that the imputed values for the 4-point Likert items remain restricted to observed response categories. The imputation model will include treatment assignment, timepoint-specific observed item values, baseline scores, and related outcome items as predictors. The primary preparedness score will be calculated within each imputed dataset only after item-level imputation. We will generate 50 imputed datasets to reduce Monte Carlo error, and results will be combined across imputations using Rubin’s rules.

To evaluate how app engagement and module completion influence efficacy, the main ITT analyses will be supplemented by an exploratory per-protocol analysis. App engagement will be operationalized as binary module completion (completing all 4 modules vs fewer than 4 modules). In the per-protocol analysis, an unconstrained linear mixed model analogous to the primary model will be fit, restricting the intervention group to “high engagers” (participants who completed all 4 educational modules), and comparing them with the full waitlist control group. An exploratory dose-response analysis will also be conducted by examining the association between the number of completed modules (0 to 4) and the 12-week preparedness score within the intervention arm using an unconstrained linear mixed model analogous to the primary analysis. Because intervention adherence is not randomized, these analyses will be considered exploratory; the cLDA constraint of equal baseline means will not be imposed, and results will be interpreted cautiously.

Exploratory analysis of the 24-week assessment will evaluate the maintenance effects among participants originally randomized to HeartBot II and within-group changes after they receive the intervention. Because the waitlist control group receives the intervention after week 12, 24-week between-group comparisons also lack randomized control protection. Therefore, exploratory analysis of all available repeated measurements (baseline, 12 wk, and 24 wk) will be conducted using an unconstrained linear mixed model with a participant-specific random intercept and fixed effects for treatment group, timepoint, and their interaction. Because treatment exposure is no longer randomized after week 12, these analyses will be considered exploratory and descriptive rather than confirmatory.

Exploratory secondary outcomes will be analyzed using methods appropriate to their scale and distribution. Continuous secondary outcomes will be analyzed using linear regression or linear mixed models, as appropriate to the timing of measurement. Binary or categorical secondary outcomes will be analyzed using generalized linear models or generalized linear mixed models.

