#### Mobile HeartBot II App

The HeartBot II intervention will be delivered through a mobile app available for both iOS and Android operating systems. The iOS version will be distributed via the Apple app store, and the Android version will be distributed via the Google Play Store. Participants randomized to the intervention group will be provided with direct download links to the appropriate app store as part of the intervention onboarding process.

Figure 2 presents screenshots of the HeartBot II app interface. After downloading the app, participants will be required to enter a unique access code to activate the app (Figure 2A). This access code will be generated by the research team and is provided only to individuals who have successfully completed the eligibility screening, consent form, and baseline survey. The access code will serve as an authentication mechanism to restrict app access to enrolled participants and to ensure that intervention exposure is limited to study participants.

Upon entering the access code, participants proceed to the registration screen, where they will be asked to enter their assigned study identification number and email address. These identifiers will be used solely for study management purposes and allow the research team to securely link participants’ app-based interactions and module completion data with survey data collected through REDCap. No personally identifiable information beyond the study email is displayed within the app.

Following successful registration, participants are directed to the app home screen, which provides an overview of the study procedures and displays the 4 HeartBot II educational modules (Figure 2C). Each module contains a chatbot focused on a specific topic related to women’s heart health. Modules are unlocked sequentially according to the study timeline, and participants can clearly see which modules are available, upcoming, or completed. To promote timely module completion and improve adherence, participants will receive automated notifications when a new HeartBot II module becomes available. Notifications will be delivered via both app push notifications and email.

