#### 12- to 24-Week Period

Following the completion of the 12-week online survey, participants in the intervention group will enter a maintenance phase and will not receive further chatbot interactions. In addition, they will receive weekly SMS text message reminders reinforcing key heart attack knowledge and prompting completion of the final online survey at week 24. The waitlist control group will begin the HeartBot II intervention, following the same 4 modules schedule as the intervention group starting at week 12. They will receive the same instructions and reminders throughout the 12- to 24-week period. At week 24, all participants will complete the final online survey. For the intervention group, this represents a follow-up assessment three months postintervention; for the waitlist control group, it represents the follow-up assessment 3 weeks postintervention. If all participants complete all study requirements, they will receive a US $20 Amazon e-gift card. To minimize the burden on participants’ time, all study procedures will be done online remotely. Data collected during the surveys will be captured on the REDCap system.

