#### Multiplicity and Gatekeeping Procedure

To control the family-wise error rate, a hierarchical gatekeeping procedure will be used for the primary and key secondary outcomes. First, the group-by-time interaction for the heart attack response preparedness score will be tested at a two-sided alpha level of 0.05. Only if the primary outcome is statistically significant will the four individual component items be formally tested as key secondary outcomes. *P* values for the four key secondary outcomes will be adjusted using the Holm-Bonferroni step-down procedure. All other secondary outcomes will be treated as exploratory; analyses will be descriptive or inferential, as appropriate, with nominal p-values reported without adjustment for multiplicity.

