#### Power and Sample Size

This study is powered based on a total analyzed sample of n=160 (80 per group). To account for a conservative 20% attrition, we will enroll a total of 200 participants. Statistical power was estimated via Monte Carlo simulations (5000 iterations) using an empirical covariance matrix and response thresholds derived from pilot data [18]; code is provided in Multimedia Appendix 1. The simulation uses the same cLDA analysis framework described above for analysis.

For the primary outcome, the heart attack response preparedness score, the study provides 90% power to detect a raw mean difference of 0.37 points on the 1‐4 scale (Cohen *d*=0.51). This detectable effect is smaller than the within-group mean change observed in pilot data (0.78 points), although the pilot study did not include a control group [18]. For the four key secondary item-level outcomes, power was also evaluated under the prescribed hierarchical gatekeeping procedure with Holm-Bonferroni adjustment. Under this framework, the study has 90% power to detect at least one significant key secondary item for a raw difference of 0.43 (*d*=0.59). To detect significant effects across all four key secondary items (assumed to have the same effect), larger effect sizes are required; 90% power is achieved at a mean difference of 0.62 points (*d*=0.85).

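### The stated imputation predictors leave out the number of modules completed, which attenuates the dose-response slope if imputed data are used and may bias the ITT estimate

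*Protocol article*

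**What the plan says.** The Statistical Analysis section handles missing data by chained-equations imputation with predictive mean matching at item level, 50 datasets and Rubin's rules. It does not limit this to the primary analysis. On the predictors it says: "The imputation model will include treatment assignment, timepoint-specific observed item values, baseline scores, and related outcome items as predictors". Engagement with the app is not named.

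The same section uses engagement twice afterwards. The per-protocol analysis keeps only intervention women who finished all four modules. The dose-response analysis is described as "examining the association between the number of completed modules (0 to 4) and the 12-week preparedness score within the intervention arm". Both are labelled exploratory. The section does not say whether they run on imputed or observed data.

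The variable is available. The Mobile HeartBot II App section says that registration identifiers let the team link app interactions and "module completion data with survey data collected through REDCap". It is therefore known for women who do not answer at week 12. Under Waitlist Control Group, controls have no access to the program before week 12, so their count is zero.

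**The concern.** An imputation model should contain every variable in the analysis model that will use the imputed values. Here the week-12 score would be imputed without regard to modules completed and then regressed on modules completed. Imputed women carry no relation between the two beyond what the baseline and other items convey, so any true slope is diluted.

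A second, conditional issue touches the primary estimate. A HeartBot participant who did little and skipped week 12 would be imputed from arm-mates who did answer. If those arm-mates completed more modules, and completion matters for the outcome, the imputed values are off. Because module exposure before week 12 exists in one arm only, the error would not cancel between arms.

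**Working it through.** **Reproducing the plan's figure.** The Multiplicity section says the primary comparison "will be tested at a two-sided alpha level of 0.05", and Power and Sample Size says "the study provides 90% power to detect a raw mean difference of 0.37 points" (d = 0.51) with 80 analysed per group.
- Implied SD = 0.37 / 0.51 = 0.725.
- SE of the difference = 0.725 × √(2/80) = 0.115; power = Φ(0.37/0.115 − 1.96) ≈ 0.897, against the stated 0.90.
- Enrolment: 160 / (1 − 0.20) = 200, as stated.
- SE implied by 90% power: 0.37 / (1.960 + 1.282) = 0.114.

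**Assumptions, none of them in the article.** Baseline to week-12 correlation is 0.5. Modules completed in the HeartBot arm are 0, 1, 2, 3, 4 with probabilities 0.10, 0.08, 0.10, 0.12, 0.60. Week-12 missingness is 20% in controls. In the HeartBot arm, by module count 0 to 4, it is:
- unrelated: 20% throughout;
- moderate: 45, 35, 30, 22, 12%;
- strong: 80, 50, 35, 20, 5%.

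Overall missingness in that arm is then 20.0%, 20.1% and 20.9%, close to the article's 20% planning figure.

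**By hand, benefit proportional to modules.** Mean modules = 0.08 + 0.20 + 0.36 + 2.40 = 3.04, so a 0.37 effect means 0.37/3.04 = 0.122 points per module.
- Slope, unrelated dropout: the imputed fifth carries no module relation, so the expected slope is 0.80 × 0.122 = 0.097.
- ITT, moderate dropout: mean modules among responders = (3.04 − 0.455)/(1 − 0.201) = 3.24. Non-responders are imputed as if from that group, so the arm mean is raised by (3.24 − 3.04) × 0.122 ≈ 0.024.
- ITT, strong dropout: (3.04 − 0.302)/(1 − 0.209) = 3.46, giving (3.46 − 3.04) × 0.122 ≈ 0.051.

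**Simulation.** 400,000 participants, normal regression imputation of the total score, and baseline-adjusted estimates standing in for cLDA. Each cell shows full data / modules omitted / modules included.

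| Benefit | Dropout | ITT | Slope per module |
|---|---|---|---|
| Proportional to modules | unrelated | 0.367 / 0.368 / 0.367 | 0.1223 / 0.0982 / 0.1223 |
| Proportional | moderate | 0.368 / 0.394 / 0.369 | 0.1226 / 0.0810 / 0.1225 |
| Proportional | strong | 0.367 / 0.418 / 0.366 | 0.1209 / 0.0504 / 0.1209 |
| Half depends on modules | moderate | 0.372 / 0.384 / 0.370 | 0.0610 / 0.0393 / 0.0608 |
| Half depends on modules | strong | 0.369 / 0.397 / 0.370 | 0.0620 / 0.0249 / 0.0632 |
| Same for all counts | moderate | 0.370 / 0.369 / 0.370 | about 0 throughout |
| Same for all counts | strong | 0.368 / 0.371 / 0.368 | about 0 throughout |
| Low completers do better | moderate | 0.367 / 0.356 / 0.367 | −0.0488 / −0.0319 / −0.0489 |
| Low completers do better | strong | 0.369 / 0.348 / 0.369 | −0.0507 / −0.0217 / −0.0495 |

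With proportional benefit the slope keeps 0.0982/0.1223 = 80%, 0.0810/0.1226 = 66% and 0.0504/0.1209 = 42% of its full-data value. The per-protocol estimate falls from 0.486 to 0.463 under unrelated dropout and by less than 0.01 in the other two proportional scenarios. With no treatment effect and modules not prognostic, the ITT estimate stays at zero, so this route does not add false positives.

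**The case against.** **The list may be condensed.** A statement of what the imputation model will include does not say that nothing else enters, and auxiliary variables are often left to an analysis plan that is not shown. That is fair. But the article states a list, and following it gives the result above. If a fuller plan already has module count, saying so closes the point.

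**The dilution is conditional, and the analysis is exploratory.** The datasets for the dose-response model are not named. In the simulation, observed cases gave an undiluted slope (0.121 to 0.123) when benefit was proportional and dropout depended only on modules. This stands, which is why the claim is limited to use of the imputed data. Since imputation is described without restriction, that use is the natural reading.

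**The ITT effect is small against the trial's precision.** This also stands: 0.05/0.114 is under half a standard error, and that is the largest scenario. Proportional benefit may also be generous, because the four primary items match modules 1 and 2 better than modules 3 and 4. With benefit from modules 1 and 2 only, the upward shift is about 0.02 (moderate) and 0.04 (strong).

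**The simulation is not the planned method.** It imputes a continuous total by regression, not four ordinal items by predictive mean matching. Recovery with module count added is expected when dropout depends only on modules, as assumed here. The figures show direction and order of size only.

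**Conclusion.** The omission is real as written and worth correcting. Using the imputed data for the dose-response model shrinks any non-zero slope: by about 20% at the planned attrition even if dropout has nothing to do with engagement, and by about 34% or 58% under the moderate and strong dropout patterns with proportional benefit.

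A reader might infer that the ITT effect is biased upward. The article does not support that. It reports no dropout by engagement or arm and no benefit by module; its only attrition figure is the overall 20% used for planning. Upward bias of about 0.01 to 0.05 points requires low completers both to miss week 12 more often and to gain less. If either condition fails the bias is about zero, and if low completers do better it is about −0.01 to −0.02.

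Two further inferences are not supported. One is that listing treatment as a predictor forces equal baseline slopes across arms: the article neither describes a single pooled model nor excludes interactions, and no harm has been quantified. The other is that the payment rule, "If all participants complete all study requirements, they will receive a US $20 Amazon e-gift card", removes the reason to answer week 12 once a module is missed: the article does not define those requirements as including modules. Changing the payment would also alter incentives mid-trial, with 86 women already enrolled.

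**What to change.** Impute separately by randomised arm, and add number of modules completed by week 12 as a predictor in the HeartBot arm. The count is zero for every control, so it carries no information there. State that the dose-response and per-protocol analyses use these same datasets. Module count enters only the imputation step; the primary cLDA model and its ITT contrast are unchanged.

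No new data are needed, and the change can be prespecified before analysis begins in spring 2027. The cost is slightly wider intervals and possibly thin donor pools for predictive mean matching. With 100 women in the arm, 10% at zero modules and 80% of those missing, only 100 × 0.10 × 0.20 = 2 such women would be observed at week 12. The number of week-12 responders at each module count should be reported beside the results.

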### HeartBot II Development and Description Used in This Study

HeartBot II is an interactive, AI chatbot built on the Google Conversational Agents platform using an LLM, specifically gemini-2.5-flash, designed to simulate natural and human-like conversations. The system is designed to follow a script similar to that used in HeartBot I, but the use of an LLM allows it to be more natural and responsive in a wider range of conversational situations. The HeartBot II intervention will be delivered through a mobile app, allowing participants to engage with the chatbot at their convenience on their smartphones.

Table 1 provides an overview of the four modules of HeartBot II conversation contents. The HeartBot II intervention consists of four modules, to be completed sequentially over a 9-week period: module 1 (overview) at week 0, module 2 (women’s heart attack symptoms) at week 3, module 3 (risk factors) at week 6, and module 4 (prevention) at week 9. Each module takes approximately 10 to 15 minutes. Module 1 covers foundational education on heart attack, emphasizing the importance of early recognition and symptoms. Module 2 emphasizes the distinct symptoms that women often experience and the importance of a timely response. Module 3 addresses modifiable and nonmodifiable risk factors for heart disease. Module 4 focuses on prevention strategies such as physical activity and diet. Each module begins with a brief introduction and informs the user about what to expect in the conversation. For participant safety, the introduction message includes the following medical emergency notice at the start of each module: “If you are experiencing a medical emergency, please call 911 immediately.”

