### Intervention Versus Waitlist Control

#### Waitlist Control Group

The waitlist control group will not receive the HeartBot II intervention during the initial 12-week period, but will receive an SMS text message once a week for 12 weeks for attention control. These text SMS messages do not include any educational content related to heart attack or heart health and are limited to neutral study reminders and general self-report prompts. For example, at week 3, participants will receive the following message: “Hi! How would you rate your overall health on a scale from 1 to 8? 1 means very poor, and 8 means excellent. Please reply with one number.” In week 9, participants will receive the following message: “Hi! You’ve reached Week 9 of the study. Thank you for staying involved. You will download the study app at Week 12 and use it four times. For now, please text us your biggest current health concern (for example, high blood pressure or weight gain).” Following completion of the week 12 outcome assessments, participants in the waitlist control group will initiate the HeartBot II program, delivered identically to the intervention group.

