#### Blinding

Because of the behavioral nature of the intervention, participants cannot be blinded to group assignment. However, they will not be informed of the specific study hypotheses or primary outcome measures. The randomization sequence will be generated and implemented in REDCap by a staff member not involved in recruitment, intervention delivery, or outcome assessment. Investigators and research staff will remain blinded to allocation sequence and block sizes. Outcome data are self-reported via REDCap.

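### Both exploratory engagement analyses condition on post-randomisation module completion; an estimate that uses the randomised arm should be prespecified beside them

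*Protocol article*

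**What the plan says.** The Statistical Analysis section gives the purpose: "To evaluate how app engagement and module completion influence efficacy, the main ITT analyses will be supplemented by an exploratory per-protocol analysis". Engagement is dichotomised: "App engagement will be operationalized as binary module completion (completing all 4 modules vs fewer than 4 modules". The per-protocol contrast keeps only the intervention women who reached that threshold, "participants who completed all 4 educational modules), and comparing them with the full waitlist control group", in a linear mixed model without the baseline constraint. A second analysis relates the number of modules completed (0 to 4) to the week-12 score within the intervention arm. The section names no covariate adjustment, weighting or complier estimate for either.

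The same paragraph carries its own caveats: "Because intervention adherence is not randomized, these analyses will be considered exploratory", and "the cLDA constraint of equal baseline means will not be imposed, and results will be interpreted cautiously".

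Two features of the design matter here. On control access, the Waitlist Control Group section says: "The waitlist control group will not receive the HeartBot II intervention during the initial 12-week period". On the outcome, the score is self-reported and the Blinding section says that "participants cannot be blinded to group assignment".

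**The concern.** The completer contrast filters one arm on a behaviour seen only after randomisation and leaves the other arm whole. Women who finish four modules over nine weeks are compared with a waitlist arm that mixes women who would have finished with women who would not. If whatever makes a woman finish also makes her self-rated confidence rise more over 12 weeks, the contrast is non-zero even when the chatbot does nothing. The within-arm dose-response analysis has the same weakness: women with four modules are compared with women who stopped early, with no randomised comparator.

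At stake is the answer to the stated engagement question, not the trial's main conclusion. Neither planned engagement analysis uses randomisation, although the design permits one that does: the waitlist arm has no app before week 12, so non-adherence is one-sided.

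**Working it through.** **The plan's own figure.** The Power and Sample Size section gives 0.37 points as d = 0.51, so the implied SD is 0.37/0.51 = 0.725. With 80 per group and two-sided alpha 0.05, power is Φ(0.51 × √(80/2) − 1.96) = Φ(1.27) = 0.897, against the stated 90%; and 160/0.80 = 200. These reproduce and are not in question. The article gives no figure for the engagement analyses.

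**Assumed inputs, not in the documents.** A latent engagement trait T with SD 1. A woman completes all four modules if T plus independent unit-variance noise exceeds −0.6. T has correlation g with the week-12 score and b with the baseline score, and the SD is 0.725 at both times. The true effect is zero.

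**Step 1: completers' mean trait.** The threshold on the standardised sum is −0.6/√2 = −0.424. The completion share is Φ(0.424) = 0.66. Completers' mean T is (1/√2) × φ(0.424)/0.66 = 0.39.

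**Step 2: bias of the completer contrast.** Without the baseline constraint, the time-by-group contrast is a difference in mean change, so bias = 0.725 × 0.39 × (g − b).

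| Trait and baseline score | g = 0.1 | g = 0.2 | g = 0.3 |
|---|---|---|---|
| b = 0 | 0.028 | 0.056 | 0.084 |
| b = g/2 | 0.014 | 0.028 | 0.042 |
| b = g | 0 | 0 | 0 |
| b = g + 0.1 | −0.028 | −0.028 | −0.028 |

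A simulation of 2 million women per arm gave 0.028, 0.058 and 0.083 for the first row. That row is 8% to 23% of the 0.37-point detectable difference.

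**Step 3: a harsher assumption.** Here motivation alone decides completion, the share is 50% to 80%, and motivation acts on the week-12 score only, at 0.2 to 0.4 SD per SD. In 20,000 simulated trials with 80 per arm, the spurious contrast was 0.05 to 0.23 points with nominal rejection rates of 7% to 40%. The ITT test stayed at about 5%, and ITT divided by the completion share stayed at about zero.

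**Step 4: which instrumental-variable estimate.** Dividing the ITT difference by the all-four completion share p is valid only if one to three modules have no effect. The intervention description says otherwise: "Module 1 covers foundational education on heart attack, emphasizing the importance of early recognition and symptoms". Table 1 places symptoms, first action, calling 911 and time to seek help in module 1 and returns to them in module 2; these are what the four outcome items ask about. If women short of four modules gain a fraction f of a true effect of 0.37, the estimate is too high by 0.37 × f × (1 − p)/p. At p = 0.66 that is 0.05, 0.09 and 0.19 for f = 0.25, 0.5 and 1. The last two exceed the largest bias in the table.

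**Step 5: precision.** The ITT standard error is about 0.725 × √(2/80) = 0.115, before any gain from baseline. For an illustrative ITT of 0.30 with 70% completing at least module 1, the estimate is 0.30/0.70 = 0.43 with standard error 0.115/0.70 = 0.164. The ratio is 2.6 either way, so it is essentially the ITT test on another scale.

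**The case against.** The authors have largely anticipated this. They call the analysis exploratory, make it a supplement to ITT, state that adherence is not randomised, and drop the baseline constraint for that reason. Formal testing covers only the primary score and its four items, so no alpha, sample size or confirmatory claim depends on it. That stands, and it limits the weight of the point.

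Dropping the constraint also does real work. As the table shows, it cancels any trait difference that is the same at baseline and week 12. A reader might infer that the bias must favour HeartBot II. The documents do not support that: the sign depends on whether the trait is tied more closely to the week-12 score or to baseline, and on a bounded 1 to 4 scale this is not known in advance. Favouring the intervention is likely, not certain. The first-row values are also smaller than one ITT standard error (0.115).

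A reader might further infer that a complier estimate based on all-four completion should replace the per-protocol analysis. Step 4 shows that it could be worse. Nor is the instrument beyond doubt: the app has a References tab with educational links, and participants know their arm when rating themselves, so assignment may act outside module use.

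What remains is that a caveat does not correct a point estimate, and that an estimate using randomisation is available from data already collected.

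**Conclusion.** The point holds as an improvement to a supplementary analysis. Both engagement analyses condition on post-randomisation behaviour and can show a benefit that comes from who completes. Under the stated assumptions, the completer contrast with no true effect is about 0.03 to 0.08 points if the trait relates to the week-12 score only, and about zero if it relates equally to baseline. The harsher assumption in step 3 gives up to 0.23. Completion share and trait strength are assumptions throughout, and the within-arm dose-response analysis was not quantified.

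Nothing here touches the primary ITT comparison. A reader might take the finding as a flaw in the efficacy inference, but the plan's labelling and its gatekeeping procedure rule that out.

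**What to change.** - Keep the completers-versus-waitlist contrast as description only, and say that it does not estimate efficacy under full adherence.
- Prespecify, beside ITT, an instrumental-variable estimate (for example two-stage least squares) with randomised arm as instrument and baseline score as covariate. Use either the number of modules completed by week 12 (0 to 4), read as an average per-module effect, or completion of at least module 1. Do not use all-four completion. Do not multiply the per-module figure by four: modules 3 and 4 mainly cover risk factors and prevention, so a linear dose effect is doubtful.
- State the exclusion assumption, that assignment has no effect outside module use, and name the References tab and unblinded self-report as the reasons it may fail.

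The cost is a few lines of code. The article says that module completion is linked to the survey data, and it expects follow-up to end by March 2027, so the change can still be made before analysis. The downside is precision: the standard error is about the ITT standard error divided by the completion share (or by the mean number of modules for the count version), and the test is essentially that of ITT, so this rescales the ITT evidence rather than adding to it.
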